### Ethical Considerations

This study has been approved by the Pennsylvania State University Institutional Review Board (IRB; STUDY00019075), and Arizona State University is an IRB-approved participating site (SITE00001437). All members of the study team have appropriate CITI training certifications. Any and all changes made to the protocol will be communicated to participants and other relevant individuals or parties immediately. All study participants provide their informed consent prior to enrollment into the study with the option to decline enrollment or stop participation at any time. Data collected are deidentified, and access is only granted through lock and key as well as secure accounts with passwords. Participants are compensated up to US $250 in gift cards for either Target or Walmart. Compensation is provided based on the completion of study milestones, such as completing the pre- and postintervention assessments, allowing electronic health record data to be extracted, and attending and completing more than 85% of study sessions and the measurement protocol. Both the intervention and control group participants can receive the same amount of compensation. This study is registered at ClinicalTrials.gov (NCT05807594).

### Randomization Procedures

A trained staff member randomizes each participant after the preintervention measures via a randomization module in REDCap [88]. The study’s biostatistician has developed the randomization scheme using variable-size random permuted blocks to ensure the number of subjects in each group is balanced after each set of *B* randomized subjects, where *B* is block size. The biostatistician programs the REDCap module, and the remaining study staff do not have access to the randomization scheme. Randomization to control (n=72) and intervention (n=72) groups uses 1:1 allocation; subjects are entered consecutively. Randomization is stratified by prepregnancy BMI status (<29.9 vs ≥30 kg/m^2^). A staff member calls each woman to inform her of study assignment. She is then provided with study information and education materials for her group assignment. The investigator is blinded to intervention assignments.

### Treatment Conditions

#### Intervention Condition

Women randomized to the intervention group receive the HMZ 2.0 intervention, described in detail above in the section “HMZ 2.0 Intervention Description,” which includes the baseline intervention (education, personalized behavior coaching or counseling, goal setting or action planning, and self-monitoring) and adaptive intervention dosage changes (for the participants who need them). This baseline intervention continues through the duration of the study. Each week over the course of the study, GWG is monitored and evaluated against the recommended upper and lower bounds of the IOM GWG guidelines [1]. Depending on each participant’s response to the baseline intervention (eg, GWG within or above guidelines) and her forecasted GWG, the automated control system may recommend a dosage change to adapt the intervention. This adaptive dosage begins after the first 4 weeks of the baseline intervention (to allow the participants to get used to the intervention and reduce burden) and includes EI and PA active learning interactive components that “step-up” the intensity of the dosage. Dosage change recommendations are automatically delivered through the HMZ 2.0 digital platform (architecture of the platform is described above); staff implement the recommended dosage change with the participant. As illustrated in Figure 6, there are up to five dosage “step-up” adaptations that can be recommended by the automated control system to regulate GWG.

**Figure 6 figure6:**
[figure not shown]
Healthy Mom Zone (HMZ) 2.0 digital platform architecture and website examples. API: application programming interface; HMPC: hybrid model predictive controller.

#### Attention Control Condition

Consistent with guidelines for comparator groups [106], all women in the study receive prenatal care offered by recruitment sites with routine provider visits, counseling about prenatal behaviors (eg, no smoking), and clinical oversight of health. To match attention to the intervention group, women in the control group receive (for the first 4 weeks of the study) one-on-one weekly education sessions delivered by trained study staff, and thereafter, they receive monthly education content delivered as asynchronous videos and get check-in support from study staff (eg, phone, text, and email) for the remainder of the study. Content includes topics, such as preparing for labor or delivery; benefits of behavioral pain management strategies (eg, mindfulness-based relaxation, imagery, music, massage, and deep breathing) to regulate pain after childbirth with nonpharmacological approaches [107]; and baby or child safety, health and development, behaviors, and nutrition. Content is drawn from evidence-based guidelines and materials designed by members of the study team for a patient-provider toolbox to reduce opioid pain management use after childbirth [107], as well as The American Academy of Pediatrics, The March of Dimes, The Centers for Disease Control, and The American College of Obstetrics and Gynecology [108-111]. The matched control group education content is also provided to the intervention group as supplemental material.

Both the intervention and control groups receive the same measurement protocol and frequency of measurement to understand and compare the impact of the intervention on primary and secondary study outcomes. Data are collected from each participant daily (GWG: Aria Wi-Fi scale [112]; PA, sedentary behavior, or sleep: Fitbit Charge 6 monitor [112], logs for device wear time, and PROMIS Sleep Disturbance [113,114] assessment; and self-reported hydration behaviors); weekly (self-reported online in REDCap; social cognitive determinants and EI diet quality: MyFitnessPal app on 2 weekdays and 2 weekend days) [19,115]; and monthly (self-reported online in REDCap; eating behaviors [19,116,117], psychosocial measures, cognition, pain, and temperament measures).

### Control Optimization Trial Procedures

Control systems methodology [51-54] in a novel Control Optimization Randomized Controlled Trial (RCT) [51] is used to test the efficacy of the enhanced HMZ 2.0 intervention with a novel digital platform and a new automated control system to regulate GWG and influence secondary outcomes. This idiographic approach uses individual dynamic models (integrating behavioral and energy balance models) informing how each woman responds to HMZ 2.0 to make personalized decisions about intensifying dosages to regulate GWG. We are not aware of any other studies using this unique strategy to regulate GWG. Women start the intervention with an “open-loop” experimentation phase and receive the HMZ 2.0 baseline intervention (dosages are not yet adapted during this time). Semiphysical models estimated using concepts from system identification [85,118-120] allow individual energy balance and behavior models to be built for each subject [51]. Model and dosage personalization is further enhanced by leveraging our team’s expertise in time-varying dynamic systems (systems that show changes in statistical properties over time) and multilevel models that integrate individual- and group-based dynamics and missing data issues [56-68]. Model components are measured with real-time data procedures to predict corresponding deviations from each woman’s target GWG range: overweight, 6.8-11.3 kg total and 0.23-0.32 kg/wk; obese, 5.0-9.1 kg total and 0.18-0.27 kg/wk [1,2]. Model estimation is used to confirm individual models and identify if certain constructs provide maximum impact for the control system. The goal of this open-loop phase is to arrive at a set of personalized dynamic models that capture the effects of dosage augmentations, gestational age, and the baseline intervention. Once the models are identified and the controller commissioned, models will not be updated, but the tuning parameters can be adjusted, if necessary. While there is no set threshold of data compliance for building individual models (models can be built with as little as 50% missing data handled with maximum likelihood estimation) [56-68], we will rely on strategies to achieve high compliance (90%; 10% missing data) similar to that in our feasibility study [19].

These personalized individual energy balance and behavior models are used in the “closed-loop” experimentation phase for the rest of the study period during which a woman’s responsivity to HMZ 2.0 is considered and dosages are adapted to regulate GWG. Continuous mHealth data are automatically linked to the control system, which considers GWG over a prediction horizon to minimize discrepancies between a woman’s observed GWG and her goal [1,2]. It considers the anticipated rate of GWG change as predicted with the individual model. Currently trained with data from the feasibility trial [19] and pilot data collected on HMZ 2.0 participants, the control system uses the values of each woman’s modifiable factors (eg, PA or EI kcals) in the current week to simulate ways in which these behaviors can be “controlled” or altered to drive GWG closer to the goal in the following week. We are cognizant of potential system identification issues that may arise with limited data available from each subject. If needed, selected parameters from the energy balance models can be constrained to be invariant across subjects to borrow strengths from other subjects and aid model estimation [121,122]. We will identify the optimal balance between control system performance (how well it can produce desired effects as efficiently as possible) and robustness (how well it can produce desired performance under disturbances and uncertainty; eg, poor compliance, change in responsiveness to dosages, and measurement variability) [10,51]. The controller has tuning parameters that allow adjustment of how fast or slow the control system makes recommendations to enable a judicious balance between effectiveness and responsiveness. Computations are performed with toolkits in MATLAB (MathWorks) and IBM ILOG CPLEX Optimizer. Study staff work with subjects to address concerns or technical issues. We will also explore how the individual subject data may inform modifications to the maternal energy balance and behavior model [10,19] and infant birth weight model [11,18].

### Primary and Secondary Outcomes

Table 1 summarizes the HMZ 2.0 measurement protocol and timepoints. More details of the primary and secondary outcomes are provided below.

**Table 1 table1:** Healthy Mom Zone 2.0 measurement protocol and timepoints.

Variable measure				Timepoint
**Energy balance model outcomes**				
	**GWG^a^** **/weight (primary outcome)**			
		High precision adult scale (10 s)	Pre- and postintervention	
		Aria Wi-Fi Smart Scale (15 s)	Pre- and postintervention and daily	
		Prenatal records: total GWG	Pre- and postintervention	
	**PA^b^** **and sedentary behavior**			
		Fitbit Charge 6: activity kcal (passive)	Pre- and postintervention and daily	
		ActiGraph GT3X: activity min (passive)	Pre- and postintervention and daily	
		PA log: monitor wear time (1 min)	Pre- and postintervention and daily	
	**Resting metabolic rate**			
		Predicted equation	Pre- and postintervention and daily	
	**EI^c^**			
		EI kcal: back-calculation method	Pre- and postintervention and daily	
		EI diet quality: MyFitnessPal app (5 min)	Pre- and postintervention and monthly	
	**PA or EI social cognitive determinants**			
		Attitude, subjective norm, perceived behavioral control, and intention (3 min)	Pre- and postintervention, daily, and weekly	
		Behavioral, normative, or control beliefs (2 min)	Pre- and postintervention and monthly	
		Retrospective self-regulation (1 min)	Pre- and postintervention, daily, and weekly	
**Secondary outcome measures**				
	**Sleep behaviors**			
		Pittsburgh sleep quality index (2 min)	Pre- and postintervention and monthly	
		FitBit Charge 6: sleep behaviors (passive)	Pre- and postintervention and daily	
		Sleep log: sleep behaviors (30 s)	Pre- and postintervention and daily	
		PROMIS Sleep Disturbance (30 s)	Pre- and postintervention and daily	
	**Eating behaviors**			
		3-factor eating inventory: cognitive restraint, disinhibition, and hunger (3 min)	Pre- and postintervention, weekly, and monthly	
	**Maternal-infant labor or delivery and adverse pregnancy outcomes**			
		Diagnoses of gestational diabetes, insulin use, preeclampsia, and depression	Postintervention only (at delivery)	
		Labor or delivery issues and other complications	Postintervention only (at delivery)	
		Infant APGAR score and mode of delivery (vaginal or cesarean)	Postintervention only (at delivery)	
	**Infant birth outcomes**			
		Birth weight (adjusted for gestational age at delivery), length, sex, gestational age at delivery, and date of birth in the electronic health record	Postintervention only (at delivery)	
**Clinical and safety protocol measures**				
	**Height**			
		Stadiometer (5 s)	Preintervention only	
	**Blood pressure**			
		Screen for preeclampsia (2 min)	Preintervention only	
	**Demographics, medical history, and obstetric history**			
		Age, race or ethnicity, income, education, medical or pregnancy history, etc (7 min)	Pre- and postintervention	
	**Depressive symptoms and monitoring health**			
		Center for Epidemiological Studies Depression Scale (3 min)	Pre- and postintervention and monthly	

^a^GWG: gestational weight gain.

^b^PA: physical activity.

^c^EI: energy intake.

### Primary Outcome

#### Participant GWG

Weight and GWG are assessed daily at preintervention, during the intervention, and at postintervention at home using the Fitbit Aria Wi-Fi Smart Scale [112] (weights are wirelessly uploaded to an online program). GWG is standardized, and the target weight gain is determined for each woman based on the BMI status (overweight, 14.1-22.7 kg; obese, 11.3-19.1 kg) [1,2]. For the criterion measure to determine when to adapt the intervention, weight gain is calculated to determine if a woman is gaining less than her goal, at the exact amount of her goal, or more than her goal. GWG over the course of the study is calculated as the last measured weight during the study subtracted by the first measured weight during the study. Weight at enrollment is measured, and prepregnancy weight and GWG from the first prenatal visit to the last predelivery weight are abstracted from clinical records.

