## Introduction

### Background

High maternal prepregnancy BMI and high gestational weight gain (GWG) elevate the risks for poor pregnancy outcomes (eg, gestational diabetes and hypertension) and fetal outcomes (eg, large for gestational age birth weight) [1-6]. High BMI and GWG may also “program” the child’s metabolism for life [7,8] and increase the future risks for obesity and type 2 diabetes in both mothers and their offspring [1-6]. As such, managing GWG has high clinical and public health significance, and it can improve maternal health and impact the etiology of obesity or diabetes in offspring at a crucial time in the life cycle [1-6,8].

Guidelines from the Institutes of Medicine (IOM) [1] and National Academy of Medicine [2] recommend that the optimal total GWG should be based on a woman’s prepregnancy BMI category (ie, overweight: 6.8-11.3 kg; obese: 5.0-9.1 kg). However, evidence from a meta-analytic review including over 1 million pregnant women found that nearly 50% of women exceeded their recommended goals [9], and this was prevalent among those with normal weight as well as those with overweight or obesity. Furthermore, data from a meta-analysis of almost 200,000 women from 25 international cohort studies in the LifeCycle Project [6] showed the highest risk for adverse outcomes among women with both high BMI and high GWG. Given these concerns as well as the rapidly changing landscape of health care delivery since the COVID-19 pandemic, there is a critical and timely need for scalable approaches to effectively regulate GWG. One such strategy that may reach more pregnant women and reduce the burden on prenatal clinicians who monitor GWG is an automated approach that relies on a digital platform with remote delivery and passive remote data collection to monitor and effectively and efficiently regulate GWG.

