Simulations to illustrate the estimated model are presented in Figure 2, which shows the Control Optimization Trial framework for the recommended dosages within the system identification phase, adhering to the 2-week and 3-week delay. The first panel displays the participant’s weight in pounds (black solid line) and the setpoint (solid magenta line), which indicates the mean of the IOM guidelines (dashed red line) [1]. Different colors are used to represent the various intervention phases. The preintervention phase lasts for 7 to 9 days (9 days in this case), followed by a 2-week baseline period. During both the preintervention and baseline phases, no augmentations or dosages are administered. The first dosage is recommended after 2 weeks in the dosage 1 phase, starting on gestational day 126. The second dosage follows 2 weeks after dosage 1 in the dosage 2 phase. The second panel contains 2 subpanels: one for the manipulated variable augmentation PA and another for PA kcal. The last panel similarly includes subpanels for augmentation healthy eating and EI kcal. The simulation results show that the hybrid model predictive controller effectively manages the participant’s weight within the IOM bounds once the controller is activated. As illustrated, both in the system identification and controller phases, recommendations for PA or healthy eating dosages lead to reduced EI (healthy eating dosage recommended) or increased PA (PA dosage recommended), ultimately facilitating weight reduction through decreased EI and increased PA.

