**Figure 4 figure4:**
[figure not shown]
Healthy Mom Zone (HMZ) 2.0 adaptive intervention design. Participant weight is measured daily and continuously evaluated against the Institutes of Medicine (IOM) gestational weight gain (GWG) ranges. All intervention women will receive the baseline intervention plus step-up 1 plus step-up 2 during the system identification open-loop experiment. Dosages 3 to 5 are delivered to selected intervention participants based on hybrid model predictive controller (HMPC) decisions in the closed-loop experiment. HE: healthy eating; PA: physical activity.

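### The target weight-gain ranges in the primary outcome section are about twice the guideline ranges given elsewhere in the protocol, so the stated criterion for adapting the intervention is wrong as written

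*Protocol article*

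**What the plan says.** The Participant GWG section, under Primary Outcome, states that "target weight gain is determined for each woman based on the BMI status (overweight, 14.1-22.7 kg; obese, 11.3-19.1 kg" and cites references 1 and 2. It then sets the rule that depends on this target: "criterion measure to determine when to adapt the intervention, weight gain is calculated to determine if a woman is gaining less than her goal". The same sentence lists the two other possible results, meeting the goal and exceeding it.

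Two other sections give different ranges from the same references. Background has "overweight: 6.8-11.3 kg; obese: 5.0-9.1 kg". Control Optimization Trial Procedures describes each woman's target range as "overweight, 6.8-11.3 kg total and 0.23-0.32 kg/wk; obese, 5.0-9.1 kg total and 0.18-0.27 kg/wk".

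Several sections link the working controller to the guideline:

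- HMZ 2.0 Pilot Study Results describes the simulation's "setpoint (solid magenta line), which indicates the mean of the IOM guidelines".
- Intervention Condition says "GWG is monitored and evaluated against the recommended upper and lower bounds of the IOM GWG guidelines".
- The Figure 4 caption gives all intervention women step-ups 1 and 2, and adds that "Dosages 3 to 5 are delivered to selected intervention participants based on hybrid model predictive controller (HMPC) decisions in the closed-loop experiment".

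**The concern.** One protocol gives two incompatible targets for the same women from the same source. The doubtful one sits in the primary outcome section, directly before the sentence on when to adapt treatment. Adaptation is the feature that this trial tests.

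Applied literally, the printed ranges set a goal that few women would exceed and most would not reach. The controller-driven dosages 3 to 5 would then rarely be called for.

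Two further rules rest on the guideline ranges: the eligibility cap of 25% of total gain (Recruitment) and the hypothesis on gain within guidelines (Goal of This Study). Both cite only the guidelines, so they would go wrong only if someone took the numbers from the primary outcome section to apply them.

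**Working it through.** **1. The two sets side by side (kg)**

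| Group | Participant GWG | Background; Control Optimization Trial Procedures | Ratio, lower limit | Ratio, upper limit |
|---|---|---|---|---|
| Overweight | 14.1-22.7 | 6.8-11.3 | 14.1/6.8 = 2.07 | 22.7/11.3 = 2.01 |
| Obese | 11.3-19.1 | 5.0-9.1 | 11.3/5.0 = 2.26 | 19.1/9.1 = 2.10 |

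The printed lower limit lies above the guideline upper limit in both groups, by 14.1 − 11.3 = 2.8 kg and 11.3 − 9.1 = 2.2 kg. There is no overlap.

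**2. Which set fits the rest of the document**

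Control Optimization Trial Procedures gives weekly rates of 0.23-0.32 kg (overweight) and 0.18-0.27 kg (obese). Weeks needed = total ÷ rate, lower with lower and upper with upper:

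- Guideline totals: 6.8/0.23 = 29.6 and 11.3/0.32 = 35.3 weeks (overweight); 5.0/0.18 = 27.8 and 9.1/0.27 = 33.7 weeks (obese).
- Printed totals: 14.1/0.23 = 61.3 and 22.7/0.32 = 70.9 weeks (overweight); 11.3/0.18 = 62.8 and 19.1/0.27 = 70.7 weeks (obese).

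Even the upper weekly rate held for 40 weeks gives 40 × 0.32 = 12.8 kg and 40 × 0.27 = 10.8 kg. Both are below the printed lower limits of 14.1 and 11.3 kg. The printed ranges are therefore the wrong ones.

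**3. Is it only a unit label?**

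Read as pounds (× 0.4536), the printed ranges become 6.40-10.30 kg (overweight) and 5.13-8.66 kg (obese). These are close to the guideline but not equal to it. A pounds-for-kilograms slip is plausible, but changing the unit alone does not recover 6.8-11.3 and 5.0-9.1 kg.

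**4. Illustration of scale**

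Assumptions: gain is normally distributed; study-period gain is set against total-gain limits; both BMI groups have the same mean. Power Calculations gives a 1.9 kg difference and a 21% relative reduction, which implies a control mean of 1.9/0.21 = 9.05 kg and an intervention mean of 9.05 − 1.9 = 7.15 kg. SDs are 4.9 kg and, in brackets, 5.7 kg, both from that section. P(gain > limit) = 1 − Φ((limit − mean)/SD).

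| At mean 9.05 kg | Overweight | Obese |
|---|---|---|
| Above guideline upper limit | 32% (35%) | 50% (50%) |
| Above printed upper limit | 0.3% (0.8%) | 2.0% (3.9%) |
| Below printed lower limit | 85% (81%) | 68% (65%) |

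- At the intervention mean of 7.15 kg with SD 4.9 kg, 20% and 35% exceed the guideline upper limit; 0.1% and 0.7% exceed the printed one.
- With the mean varied over 8-12 kg and the SD over 4.9-5.7 kg, 25-56% (overweight) and 41-72% (obese) exceed the guideline limit; 0.1-3% and 1-11% exceed the printed one.

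**5. Set point, if the printed ranges were used**

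Taking the set point as the midpoint of the range, it would move from (6.8 + 11.3)/2 = 9.05 to (14.1 + 22.7)/2 = 18.4 kg (overweight), and from (5.0 + 9.1)/2 = 7.05 to (11.3 + 19.1)/2 = 15.2 kg (obese).

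**The case against.** The best reply is that this is a reporting slip in one parenthesis. The correct values are printed twice, once in the section that describes the control system. HMZ 2.0 Pilot Study Results, Adaptive Intervention Dosage Changes, the Figure 4 caption and Intervention Condition all tie dosing to the guideline. Read as pounds, every printed limit falls within about 1 kg of the guideline, and the pilot simulation plots weight in pounds. On this view nothing in the trial has gone wrong. Most of this stands: a text error is the likeliest explanation, and no section shows that the printed values were coded.

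A second objection is that the percentages above are not trigger rates. The controller acts on forecast gain during pregnancy, not on final gain. The 9.05 kg mean belongs to the control arm, which gets no adaptive dosages, and a common mean for both BMI groups is unsupported. This also stands. The figures show only how far apart the two sets of limits are; the lack of overlap proves the error without them.

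A third is that the primary comparison and power are untouched and that insufficient gain is monitored under separate criteria (Safety Considerations). That is correct and limits the consequences.

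None of this removes the contradiction. The wrong values stand next to a stated criterion for changing treatment, and anyone who codes or replicates the trial from the primary outcome section would take them.

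**Conclusion.** The concern holds. The target ranges in Participant GWG are 2.0 to 2.3 times the guideline ranges stated elsewhere from the same references, do not overlap them, and cannot be reached at the protocol's own upper weekly rates over 40 weeks. The adaptation criterion that uses them is wrong as written. This conclusion rests only on figures printed in the document and, for the rate check, on 40 weeks as a generous length of gestation.

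Whether any woman's treatment is affected depends on which values were coded, and the document does not settle that. If the printed values were in use, dosages 3 to 5 would be nearly switched off; the size of that effect is illustrative and depends on the assumptions listed with the calculation. The comparison of mean gain between groups, the sample size of 144 and the power statement do not depend on these ranges.

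**What to change.** Correct the Participant GWG section to 6.8-11.3 kg (overweight) and 5.0-9.1 kg (obese), checked against the cited guideline. Confirm that the controller, the 25% eligibility rule and the within-guideline outcome are coded with those values. Re-check women already enrolled (12 at publication, per Results) only if that audit finds the wrong values in use.

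The cost is one corrected line and a configuration check. No added participants or procedures are needed.
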